### Quantitative data

Change in HbA1c before and after the intervention will be evaluated, accounting for SW-CRT design using the swCRTdesign package for R version 4.0.2 and the swSummary function [18]. The sustainability of the effects will be evaluated using the change in quarterly parameters after the intervention is completed. Differences between socio-economic strata will be compared as sub-group analyses depending on the income category of the clusters. Missing data will not be imputed.

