**Methods and analysis:**

The mixed methods study will begin with a qualitative study to evaluate the facilitators and barriers towards CL-based DSME. The in-depth interview notes will be transcribed for thematic analysis. These results will be utilized for a stakeholder’s workshop to develop the EK-DIN kit, a patient-interfacing app, and an implementation plan. Rollout will be conducted in 30 clusters in Delhi, preselected by the DEDICOM-II survey in 5 steps (6 clusters every 3 months: 2 each from each socio-economic category; randomly selected per sequence). A CL from each cluster will be trained in using the EK-DIN kit/app over 1 month. The trained CL will conduct DSME sessions among the cluster residents using the EK-DIN kits provided fortnightly for 3 months. Compliance and blood parameters data will be collected at baseline, 3 months after the intervention, and every quarter thereafter till completion. Change in HbA1c before and after the intervention will be evaluated as the primary outcome using the swCRTdesign package for R version 4.0.2 and the swSummary function. The sustainability of the effects will be evaluated using the change in quarterly parameters after intervention completion.

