## Background

Type 2 diabetes is a major public health problem, with an estimated 537 million adults worldwide. In India alone, the numbers exceed 101 million and are expected to increase to 134 million by 2045 [1]. Despite its documented high and rising prevalence, serious long-term complications, and established evidence-based guidelines for management, the translation of practice recommendations to care is still deficient [1, 2]. This, in turn, contributes to a high risk of complications, cost, and mortality.

With this background, we undertook two community surveys on the Quality of Diabetes Care and associated cardiovascular risks in Delhi in 2005–2006 [3] and, more recently, in 2018–2020 [4] (DEDICOM and DEDICOM-II; funded by ICMR). Both house-to-house 30-cluster surveys showed that the quality of diabetes care delivered to diabetes patients in Delhi was consistently poor. Although not directly comparable due to differing population sets, it is noteworthy that the percentage of subjects with extremely poor diabetes control (HbA1c > 10) was significantly higher in the second survey compared to the first one. This implied a progressively deteriorating situation and emphasized the urgent need for an effective intervention plan to address the problem.

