### Sample size considerations

The sample size was estimated using the stepped wedge cluster randomized design package (swCRTdesign) in R software (version 4.0.2) [18]. The following information was utilized from our recent DEDICOM-II survey: thirty clusters, a mean HbA1c of 8.9%, standard deviation 4.3, and an intra-cluster correlation of 0.09. Assuming an alpha error of 0.05 and a power of 0.9, it was estimated that a five-step design, using 12 subjects per cluster and with 6 clusters per sequence (2 from each stratum; a total of 360 subjects) will be required to detect a significant mean difference of 1% (~ 10 mmol/mol) in HbA1c level. The study would also be adequately powered (0.8) for comparisons between socio-economic classes with the same consideration using 2 clusters per step per strata.

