#### Expected outcomes

##### Primary outcome measure

Comparison of the HbA1c levels between the groups 3 months after the start of intervention.

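### The primary HbA1c analysis is worded as a before-after change with no stated estimator or calendar-period effect, and it matches neither the stated primary outcome nor the model behind the sample size

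*Protocol article*

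**What the plan says.** The abstract (Methods and analysis) states: "Change in HbA1c before and after the intervention will be evaluated as the primary outcome". The Quantitative data section repeats that contrast and says that it will be evaluated "accounting for SW-CRT design using the swCRTdesign package for R version 4.0.2 and the swSummary function". Neither place names a regression model, a period effect, a random effect or another estimator of the intervention effect.

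The Primary outcome measure section defines the outcome differently: "Comparison of the HbA1c levels between the groups 3 months after the start of intervention".

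The design is set out under Phase 3. Five groups of six clusters cross from control to intervention in random order, one group every 3 months, and none crosses back. Group 1 has 3 months before and 18 months after its crossover, group 2 has 6 and 15, and so on. HbA1c is measured quarterly throughout.

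The sample size section gives an SD of 4.3, an intra-cluster correlation of 0.09, 30 clusters, 12 subjects per cluster and a 1-point difference: "Assuming an alpha error of 0.05 and a power of 0.9".

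**The concern.** In a one-way stepped wedge, exposure rises with calendar time in every cluster. The randomised order protects against a time trend only if exposed and unexposed clusters are compared within the same period. A before-after change makes no such comparison. Season, laboratory drift or the effect of repeated quarterly testing would then enter the estimate in full.

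The two statements of the primary contrast do not settle the matter. One is a within-cluster change. The other is a between-group comparison at 3 months after start. At its own month 3 each cluster group is already exposed, so that comparison has an unexposed comparator only if groups still waiting in the same calendar quarter are used, and the text does not say so. Two analysts could follow this article and produce different primary results, one of them open to trend bias.

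**Working it through.** **1. Does the stated sample size imply time adjustment?**

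Inputs from the sample size section: SD 4.3, ICC 0.09, I = 30 clusters, m = 12, difference 1, power 0.90, alpha 0.05 (taken as two-sided). Assumptions: T = 6 periods for five steps, independent samples per period, random cluster intercept, one fixed effect per period (the Hussey-Hughes model).

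- Between-cluster variance τ² = 0.09 × 4.3² = 1.664.
- Cluster-period error variance σ² = 0.91 × 4.3² / 12 = 1.402.
- With X the 0/1 exposure indicator per cluster and period: U = sum of X = 90; W = sum over periods of squared period totals = 1980; V = sum over clusters of squared cluster totals = 330.
- Var = Iσ²(σ² + Tτ²) / [(IU − W)σ² + (U² + ITU − TW − IV)τ²] = (30 × 1.402 × 11.387) / (720 × 1.402 + 2520 × 1.664) = 479.0 / 5203 = 0.0921.
- SE = 0.303; power = Φ(1/0.303 − 1.96) = 0.909.

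| Model, 6 periods | Subjects per cluster | Power |
|---|---|---|
| With period effects | 11 | 0.886 |
| With period effects | 12 | 0.909 |
| Without period effects | 4 | 0.852 |
| Without period effects | 5 | 0.916 |
| Without period effects | 12 | 0.999 (SE 0.197) |

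So 12 is the smallest size reaching 90% with period effects. Without them, 5 (150 subjects) would do. With 7 or 8 periods the minimum is 11 with period effects (12 per cluster gives 0.927 and 0.939) and 4 without. Every variant without period effects is far from 12.

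**2. How far apart in time are before and after?**

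Quarterly measurement from month 0 to month 21 gives quarters 0 to 7. Group s (1 to 5) is control at quarters 0 to s and exposed at quarters s+1 to 7.

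- All data pooled within cluster: (s + 8)/2 − s/2 = 4 quarters, for every s. In general the gap is T/2, so 3 quarters with 6 periods and 3.5 with 7.
- Last pre-intervention quarter against month 3: (s + 1) − s = 1 quarter.

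A mixed model with a cluster effect but no period effects, fitted to a linear trend and a true effect of zero, is biased by 2.9, 3.4 or 3.9 times the quarterly drift with 6, 7 or 8 periods. With period effects the bias is 0.

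**3. Size of the bias**

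The article gives no drift rate, so the rates below are assumptions.

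| Drift, points per quarter | Bias, last quarter vs month 3 | Bias, 3 to 4 quarters (pooled) | Type I error of the model without period effects, 6 to 8 periods |
|---|---|---|---|
| 0.05 | 0.05 | 0.15–0.20 | 11%–22% |
| 0.10 | 0.10 | 0.30–0.40 | 31%–65% |
| 0.20 | 0.20 | 0.60–0.80 | 84%–99.7% |

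The target difference is 1.0.

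**The case against.** The strongest reply is that a reader might infer that the trial will run a naive before-after test and credit any trend to the intervention. The documents do not support that. The sentence on analysis says the stepped-wedge design will be accounted for, no passage excludes a time term, and the planned cluster size fits a time-adjusted model. A condensed article may also leave model terms to a full protocol or SAP that is not shown. All of this stands, so the bias is conditional on the wording being followed without a time term. What does not fall away is that the article states two different primary contrasts, and that the one in the analysis section is unsuited to the design unless time is adjusted for.

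A reader might also infer that swSummary is purely descriptive and so cannot deliver the analysis. The name suggests a summary, but the documents do not say what the function returns, and the package is named beside it. The point does not need that claim.

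Nor do the documents show that a trend exists or which way it runs. The Background says of its two surveys: "This implied a progressively deteriorating situation and emphasized the urgent need for an effective intervention plan". It also cautions that they covered different populations and cannot be compared directly, and the significant difference it reports concerns only the share with HbA1c above 10. A continued rise would hide a benefit; only a fall would mimic one. Regression to the mean is a weak threat here, because eligibility sets no HbA1c threshold.

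Finally, the 4-quarter gap is one reading. Comparing the last pre-intervention quarter with month 3 gives 1 quarter, and that reading fits the 3-month outcome.

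**Conclusion.** The concern holds as a badly stated primary analysis, not as proof of a biased one. The abstract and the Quantitative data section describe a before-after change without an estimator or a period effect; the primary outcome section describes another contrast; and the sample size fits a period-adjusted model that the analysis text does not carry through.

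If the before-after wording were followed without a time term, the bias would be 1 quarter's drift on the narrowest reading and about 3 to 4 quarters' drift when all data are pooled: 0.05 to 0.8 HbA1c points against a 1-point target, in either direction. This rests on an assumed linear drift of 0.05 to 0.20 points per quarter, common to all clusters. The sample-size comparison rests on the stated SD and ICC, a two-sided alpha and independent samples per period.

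**What to change.** Align the abstract, the Quantitative data section and the Primary outcome measure section to one primary contrast. Estimate it from a linear mixed model on the quarterly HbA1c values, with intervention status and categorical calendar quarter as fixed effects and random effects for cluster and participant. Keep swSummary for description only. Cluster-by-quarter effects and a small-sample correction may be worth considering, but this defect does not require them.

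The cost is wording and standard code, with no new data. Confidence intervals will be wider than for an unadjusted analysis: SE 0.303 against 0.197 with 6 periods. Under the stated inputs 360 subjects still suffice for the average intervention effect.

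If the effect at 3 months of exposure is chosen instead, recheck its power. With 8 periods, a separate effect for each exposure quarter and no participant correlation, power is 0.886. It falls to 0.82 with an assumed cluster autocorrelation of 0.8, and exceeds 0.9 in both cases if a within-participant correlation of 0.5 is assumed.

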#### Expected outcomes

##### Primary outcome measure

Comparison of the HbA1c levels between the groups 3 months after the start of intervention.

##### Secondary outcomes

These will be compared at the trial endpoint. The trial endpoint will vary from 6 to 18 months after intervention for various cluster groups, as presented in Fig. 3.

Comparison of HbA1c in the groups at “trial end point”Comparison of Lipid profile, blood pressure, drug compliance, and preventive checks between the groupsComparison of sustainability of the gains in the groups

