#### Phase 3: Implementation of the intervention (stepped wedge cluster randomized trial (Sw-CRT))

The community intervention phase of the study will begin with a pilot on 10 known diabetes subjects from a nearby locality. The information gathered through the pilot will be used to further fine-tune the rollout plan. After the pilot, the rollout will target to recruit 350 diabetes patients from among the subjects of the DEDICOM-II survey [4]. It is expected that it will be possible to recruit ~ 12 subjects per cluster from among the 20–30 subjects/cluster recruited for the earlier survey [4]. All earlier clusters and participants will be eligible for recruitment in the proposed study and will be approached for informed consent.

The intervention will be rolled out using the stepped wedge cluster randomized trial format, as summarized in Figs. 2 and 3. As presented in this design, clusters enter the intervention arm sequentially, contributing control and intervention data, unlike traditional cluster-randomized clinical trials. The design involves 5 groups of clusters (6 clusters in each group; 2 each from lower, middle, and higher strata) with sequential cluster group crossover from control to intervention until all are exposed. Each cluster group will be pre-specified based on geographical contiguity. The order of rollout in the cluster groups will be determined by a computer-generated random sequence. The sequence will be concealed in opaque sealed envelopes till use. While blinding is not considered feasible at the participant/field staff level, the laboratory processing, data entry, statistical analysis, and investigators will be blinded to the sequence of intervention.

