**Fig. 3 Fig3:**
[figure not shown]
Trial rollout sequence

As presented in Fig. 3, at Step 0, each cluster group starts as a control condition, with the first cluster group initiating the preparation phase and contributing control data. In Step 1, cluster group 1 enters the intervention period. Three months later, another cluster group (6 clusters) enters the intervention period. This process continues until all clusters enter the intervention. Hence, the stepped-wedge trial design involves 3 months of data in pre-intervention and 18 months in post-intervention conditions for cluster group 1, followed by 6 months in pre-intervention and 15 months in post-intervention conditions in cluster group 2, and so on. All 30 clusters will be completed in 5 steps. The study design has been specifically chosen due to the documented inherent sample size, ethical, logistical, and naturalistic advantages of a wedge cluster rollout [16] and to evaluate the baseline status, impact of intervention, and sustainability of any benefits achieved.

For each cluster group, participants of the DEDICOM-II survey will be invited for recruitment by the research team in accordance with the following selection criteria.

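### No cluster is unexposed at the trial endpoint, so the stated endpoint comparison of lipids, blood pressure, drug compliance, preventive checks and HbA1c cannot estimate the intervention effect

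*Protocol article*

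**What the plan says.** The Secondary outcomes section of the protocol article sets one time point for its whole list: "These will be compared at the trial endpoint. The trial endpoint will vary from 6 to 18 months after intervention for various cluster groups". The list has three items:

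- HbA1c at that time point, worded "Comparison of HbA1c in the groups at" the endpoint.
- Lipid profile, blood pressure, drug compliance and preventive checks, compared between the groups.
- Sustainability of the gains, compared in the groups.

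The Phase 3 section describes five groups of six clusters with "sequential cluster group crossover from control to intervention until all are exposed". The text under Fig. 3 gives the timing as "3 months of data in pre-intervention and 18 months in post-intervention conditions for cluster group 1", then "6 months in pre-intervention and 15 months in post-intervention conditions in cluster group 2", and so on, and adds: "This process continues until all clusters enter the intervention".

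Under Quantitative data, the stepped-wedge analysis is stated for HbA1c only: "Change in HbA1c before and after the intervention will be evaluated, accounting for SW-CRT design". Sustainability has its own method there: "The sustainability of the effects will be evaluated using the change in quarterly parameters after the intervention is completed".

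**The concern.** A stepped-wedge trial gets its controlled information from calendar periods in which some clusters are exposed and others are not yet. The secondary comparison is placed at a time when no such contrast exists. A null result would then be expected both from an intervention that works and lasts and from one that does nothing. A non-null result would reflect time since intervention or differences between the groups of clusters.

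Stated objectives depend on these outcomes. The primary objective covers biochemical parameters and preventive processes. The first secondary objective is cardiovascular risk, for which lipids and blood pressure are the relevant measures.

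**Working it through.** **Inputs.** Group 1 has 3 months before and 18 after the start of intervention, and group 2 has 6 and 15 (text under Fig. 3). There are five groups of six clusters (Phase 3 section). Continuing the pattern, group s has 3s months before and 21 − 3s months after.

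**1. Reproduce the plan's own range.** For s = 1 to 5, 21 − 3s = 18, 15, 12, 9 and 6 months. This matches the stated 6 to 18 months. For every group 3s + (21 − 3s) = 21, so the endpoint is a single calendar time, month 21.

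**2. Count unexposed clusters.** Each quarterly round is assigned to the condition of the quarter just ended, so the round at month 3s is the last pre-intervention round of group s.

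| Round (month) | Unexposed groups | Unexposed clusters (of 30) |
|---|---|---|
| 3 | 5 | 30 |
| 6 | 4 | 24 |
| 9 | 3 | 18 |
| 12 | 2 | 12 |
| 15 | 1 | 6 |
| 18 | 0 | 0 |
| 21 | 0 | 0 |

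**3. What the endpoint contrast estimates.** Write the expected outcome of group s at month t as μ + β(t) + δ·X, where β(t) is the calendar trend and X = 1 once the group is exposed. At month 21, X = 1 for all groups.

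- Between any two groups, the expected difference is δ − δ = 0, whatever the value of δ. With the protocol's mean HbA1c of 8.9%, a constant effect of −1 and no trend, every group is at 8.9 − 1.0 = 7.9%.
- In a model of the month 21 data alone, the treatment column equals the intercept, so δ is not estimable. Months 18 and 21 together give the same result.
- Endpoint minus baseline has expectation δ + β(21) − β(0). Without concurrent controls, δ cannot be separated from the trend.

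**4. If the effect is not constant (an assumption for illustration).** Let the effect wane linearly from −1.0 at 3 months to −0.5 at 18 months: −(1 − 0.5 × (d − 3)/15) at d months of exposure. For d = 18, 15, 12, 9 and 6 this gives −0.5, −0.6, −0.7, −0.8 and −0.9. The groups then differ by up to 0.4 in favour of the latest starters. That difference describes waning, not intervention against control.

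**5. What the full quarterly data can do.** The Hussey-Hughes calculation uses fixed period effects, a random cluster effect, 12 per cluster-period, total SD 4.3, ICC 0.09 and two-sided alpha 0.05 (the sidedness is assumed).

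- With six periods the standard error for HbA1c is 0.303, and power for a 1% difference is Φ(1/0.3034 − 1.960) = Φ(1.336) = 0.909, close to the stated 0.9.
- With seven quarterly periods the standard error is 0.293, and power is Φ(1/0.2929 − 1.960) = Φ(1.455) = 0.927.

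So the same trial that has no information on δ at month 21 has ample information over all rounds. These figures are for HbA1c; the article gives no inputs for the other outcomes.

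**6. How far controlled information reaches.** At month 15, group 1 has been exposed for 15 − 3 = 12 months while group 5 is still unexposed. Beyond 12 months of exposure there is no concurrent control at all.

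**The case against.** Several points on the other side have weight.

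*Sustainability is a different question.* The design was chosen partly to assess whether gains last, and Quantitative data gives sustainability its own quarterly method. For that question a contrast by time since intervention is relevant, and no difference under a constant benefit is the right answer. This stands, although the contrast still lacks a concurrent control and ties each duration to one group of six clusters. Endpoint HbA1c can also be read as a durability measure, since the effect itself is the primary outcome at 3 months.

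*The word groups is ambiguous.* The article elsewhere refers to both groups and says that clusters contribute control and intervention data. It may mean conditions rather than rollout groups, with the secondary outcomes meant to follow the stepped-wedge analysis of HbA1c. The article does not say so, and under either meaning the stated time point has only exposed clusters.

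*Secondary models belong in the SAP.* Model details do, and Fig. 3 is not shown. But the time point and the contrast are fixed in the text, and they conflict with the rollout in the same article.

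A reader might also infer more than the documents support:

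- That every secondary outcome is compared between the groups. That phrase belongs to the lipid, blood pressure, compliance and preventive-check item; HbA1c and sustainability are worded as in the groups. Cost-effectiveness and quality of life stand under a separate heading.
- That all clusters are still receiving the course at the endpoint. The fortnightly sessions last 3 months, after which monthly support continues. Exposed is the accurate word.
- That the secondary objectives cannot be answered. The cardiovascular-risk objective is not tied to the endpoint, and the quarterly data can address it.

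**Conclusion.** The comparison is wrong as written for lipid profile, blood pressure, drug compliance and preventive checks, and for any reading of endpoint HbA1c as an effect versus control. At month 21, 0 of 30 clusters are unexposed, the intervention effect is not estimable from that round, and a constant, sustained benefit has an expected between-group difference of 0. Reading the comparison as endpoint against baseline does not rescue it.

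The count rests on continuing the stated pattern from groups 1 and 2 to group 5, which the article's own range of 6 to 18 months confirms. The expected difference of 0 assumes a constant effect. The absence of a control does not depend on that assumption.

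The point does not extend to the primary outcome at 3 months or to the sample size, and it does not make the sustainability comparison invalid. The defect lies in the stated analysis, not in the data collected.

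**What to change.** In Secondary outcomes, for lipid profile, blood pressure, drug compliance, preventive checks and any claim of an HbA1c effect versus control, replace the endpoint comparison with an analysis of all quarterly measurements that accounts for the stepped-wedge design. It should include calendar-period effects, allow for clustering and for repeated measures on the same participants, use a model suited to binary outcomes where needed, and estimate exposed against not-yet-exposed cluster-periods. The article specifies no model in this detail for HbA1c, so the revision has to state it rather than refer back to one.

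Keep the endpoint and post-completion quarterly comparisons for the sustainability question, since a single exposed-versus-unexposed effect averages over exposure time. Describe them as contrasts by time since intervention without a concurrent control. Say which meaning of groups applies to each item.

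The cost is a change of wording and of analysis. The text following the Exclusion criteria has quarterly evaluations continuing in all groups, and Duration of treatment and follow-up has blood sampling, preventive-examination compliance and drug compliance recorded quarterly for all participants, so no new data are needed. The Abstract summarises the schedule more briefly; one sentence confirming that the pre-intervention rounds include all these measures would settle it.
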